## Abstract

**Introduction:**

Knee injury history and increased joint load, respectively, are major risk factors for the development of knee osteoarthritis (OA). Lower extremity muscle function, such as knee muscle strength, influence joint load and may be important for the onset of knee OA. However, the role of muscle function as a possible modifiable protective mechanism for the development of OA after anterior cruciate ligament reconstruction (ACLR) is not clear.

**Methods and analysis:**

In this prospective cohort study, 100 patients (50% women, 18–35 years) with ACLR will be recruited from Skåne University Hospital, Sweden and Oslo University Hospital, Norway. They will be assessed with a comprehensive test battery of muscle function including muscle strength, muscle activation, hop performance, and postural orientation as well as patient-reported outcomes, one year (baseline) and three years (follow-up) after ACLR. Primary predictor will be knee extension strength, primary outcome will be patient-reported knee pain (Knee injury and Osteoarthritis Outcome Score, subscale pain) and secondary outcomes include compositional MRI (T2 mapping) and turnover of cartilage and bone biomarkers. Separate linear regression model will be used to elucidate the influence of each baseline muscle function variable on the outcomes at follow-up, adjusted for baseline values. Twenty non-injured individuals will also be assessed with MRI. This study is approved by The Regional Ethical Review Board in Lund (Sweden) and Oslo (Norway).

**Discussion:**

This study may have important clinical implications for using muscle function to screen for risk of early-onset knee OA and for optimizing exercise therapy after knee injury.

## Introduction

1

An anterior cruciate ligament (ACL) injury is commonly associated with long-term functional limitations [[1], [2], [3], [4]]. In addition, it is well established that a history of knee injury is a major risk factor for the development of knee osteoarthritis (OA). A recent systematic review and meta-analysis found that a previous ACL injury was associated with a four to six-fold increased risk of developing knee OA two to 22 years post knee injury [5].

OA develops slowly. Follow-up of approximately 5–10 years is required to detect radiographic features indicative of OA such as joint space narrowing and osteophytes, i.e., features found relatively late in the disease process [6], indicating that radiography is not useful for early detection of OA [7,8]. Early detection of the disease is important as this may permit early intervention, such as load management by appropriate exercise programs, before the biomechanical derangement becomes too severe. Patient-reported pain may be used as a marker of future significant knee pain and early symptomatic knee OA in patients with ACL injury [9,10] and has also been reported to be related to features of tibiofemoral OA, such as joint space narrowing and cartilage thickness [9,11,12]. Magnetic resonance imaging (MRI) techniques, such as T2 relaxation time (a measure of water content and biochemical composition) is another promising technique that seems sensitive for detecting cartilage degeneration early (two – three years) in the disease process [13,14]. T2 is reported to be higher in the involved knee 6–24 months after injury compared to both healthy controls [15] and to the contra-lateral knee [16]. Furthermore, increased knee adduction moment [17], worse self-reported activity of daily living [16] and lower knee muscle strength [18] seem to be associated with higher T2. Thus, T2 may be a clinically important measure of early knee OA after knee injury. Molecular biomarkers may also be used to identify early OA in these patients and several biomarker candidates are under validation [[19], [20], [21]].

Knee joint load is suggested to be a contributing factor for knee OA development and progression [[22], [23], [24], [25]]. Sensorimotor function, such as muscle strength and muscle activation patterns, factors that are modifiable by training, influences the magnitude of joint load and may, thus, play an important role for the onset of knee OA [26]. Knee muscle weakness has been reported to be associated with an increased risk of developing radiographic and symptomatic knee OA in individuals without previous knee joint injury [27], whereas the evidence for such association in individuals with a knee injury is inconclusive [27,28]. A recent systematic review reported conflicting results of other measures of muscle function than knee muscle strength, such as hop performance, as contributing factors for radiographic or symptomatic OA development after knee injury [28]. Furthermore, low patient-reported function 2 years after ACLR has also shown to be associated with symptomatic and radiographic knee OA ten years post injury [28]. To our knowledge, there are no studies on the role of muscle function as a possible modifiable protective mechanism for the development of early-stage OA after knee injury, using a comprehensive test battery of muscle function as well as different measures of early knee OA. Such knowledge would help in designing more effective training interventions in the treatment of knee injury and subsequent early-onset OA. Thus, the aim of this prospective cohort study including young people with anterior cruciate ligament reconstruction (ACLR) is to study the association between different measures of muscle function and early future knee OA assessed as patient-reported pain, features indicative of early radiographic OA measured with MRI, and early detection of OA in biomarker profiles, respectively. In addition, we will investigate the prevalence of early knee OA in individuals 1 and 3 years post ACLR, respectively, compared to non-injured controls.

## Methods and analysis

2

This is a prospective cohort study adhering to the STROBE guidelines (http://www.strobe-statement.org). The study is registered on ClinicalTrials.gov (NCT03473873).

### Participant and setting

2.1

Patients will be consecutively recruited from the Department of Orthopedics, Skåne University Hospital, Sweden (main site) and the Department of Orthopedics, Oslo University Hospital, Oslo, Norway. The majority of patients (approx. 70%) will be included in Sweden. The study is approved by The Regional Ethical Review Board in Lund, Sweden (Dnr 2016/319) and Oslo, Norway (REK sør-øst D: 2016/1128).

*Inclusion criteria*: i) one year (between 10 and 16 month) after ACLR, with or without associated injuries to other structures of the knee (e.g., collateral ligament(s), meniscal injury), ii) age 18–35 years. *Exclusion criteria*: i) previous serious injury or surgery to either knee (e.g., ACL tear, meniscal tear), ii) diseases or disorders overriding the knee condition (e.g., neurological disease), iii) contra-indicators for MRI, iv) not understanding the languages of interest (any Scandinavian language or English). Possible confounders to record at the assessments include: i) additional surgery to the index knee between the time point of ACLR and inclusion and/or during follow-up, ii) serious injury to the index knee (e.g., giving-way episode(s)) resulting in pain and/or swelling and requiring inpatient or outpatient health care between the time point of ACLR and inclusion and/or during follow-up. Demographics (e.g., age sex, BMI, heredity) and other patient-reported outcomes will be collected at baseline and at follow-up (See Table 1 for full details). As a sample of convenience, 20 age- and sex-matched non-knee injured individuals will be recruited among students in Lund, Sweden. With the exception that these individuals should be free from ACL injuries to both knees, the inclusion/exclusion criteria will be the same for this cohort as for the patient cohort.

**Table 1 tbl1:** Demographics and patient-reported outcomes to be collected at baseline and at follow-up.

	Baseline		Follow-up	
	ACLR patients	Controls	ACLR patients	Controls

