### Statistical analysis

2.5

For descriptive purposes, the mean (SD), or median (quartiles), at baseline and follow-up assessments will be used as appropriate. Separate linear regression models will be used to elucidate the influence of the absolute values of each predictor on the absolute value on primary, secondary and exploratory outcomes in cross-sectional analyses and on the absolute value as well as change in primary, secondary and exploratory outcomes in longitudinal analysis, adjusted for baseline values and possible confounders (e.g., age and associated injuries). In addition, logistic regression analysis will be used to elucidate the influence of each predictor on significant knee pain (KOOS pain ≤72 vs > 72). Assuming a clinically relevant correlation of 0.30 between knee extension strength and self-reported pain [50], we need 84 patients with 80% power at the 5% significance level. Based on this calculation, we will include 100 patients including an approximate drop-out of 15%. For explorative purposes, an analysis of covariance (ANCOVA) will be used to investigate differences in the presence of early knee OA between the 100 patients with ACLR and twenty sex and age matched non-injured individuals, adjusting for activity level.

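### The exploratory ACLR-versus-control ANCOVA adjusts only for activity level, so any age or sex imbalance left by loose matching of the 20 Lund students would stay in the result

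*Protocol article*

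**What the plan says.** - **Control source (section 2.1).** "As a sample of convenience, 20 age- and sex-matched non-knee injured individuals will be recruited among students in Lund, Sweden". Apart from the requirement of no ACL injury in either knee, controls meet the same criteria as patients, including "ii) age 18–35 years". Patients are consecutive cases from two hospitals, about 70% of them from Sweden.
- **Purpose (Introduction).** A stated additional aim is that "we will investigate the prevalence of early knee OA in individuals 1 and 3 years post ACLR, respectively, compared to non-injured controls".
- **Analysis (section 2.5).** "For explorative purposes, an analysis of covariance (ANCOVA) will be used to investigate differences in the presence of early knee OA"; the comparison is "between the 100 patients with ACLR and twenty sex and age matched non-injured individuals, adjusting for activity level". No other covariate is named for this model. Age does appear in section 2.5 as an example of a confounder, but for the predictor regressions.
- **Data available (Table 1).** Age, sex, height, body mass and current Tegner activity level are collected in both patients and controls.

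**The concern.** The comparison relies on matching at recruitment to handle age and sex. Two features make that reliance fragile. The controls come only from students, so the upper part of the 18–35 range may be hard to fill. And the 20 controls are compared with the whole group of 100 patients, so the match must hold for the patients' overall age and sex distribution. The shared age criterion sets limits, not a distribution.

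If a difference in age or sex remains, it is mixed with the effect of injury and reconstruction on outcomes such as T2 or a serum biomarker. Adjusting for activity level does not remove it, except in so far as activity happens to track age or sex. Because the comparison would be described as matched, a reader would have less reason to look for this.

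**Working it through.** **The plan's own figure.** No sample-size figure is given for the controls. The only one is 84 patients for a correlation of 0.30 with 80% power at 5% (two-sided assumed). By Fisher's z:

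n = ((1.960 + 0.842) / atanh(0.30))² + 3 = 84.93, so 85. A bias-corrected version gives power 0.7996 at n = 84.

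Dividing by 0.85 for drop-out gives 99 (from 84) or 100 (from 85), in line with the stated 100. The figure reproduces, and it does not involve the controls.

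**Precision of the control comparison.** For a continuous outcome in SD units, before covariates:

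- SE = √(1/100 + 1/20) = √0.06 = 0.245 SD
- Smallest difference detectable with 80% power = (1.960 + 0.842) × 0.245 = 0.69 SD

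**Bias from an age gap that is not adjusted for.** These inputs are assumptions, because the document gives neither group's age distribution nor any outcome–age relation:

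- patient ages uniform on 18–35, so SD = 17/√12 = 4.91 years
- mean age gap g between patients and controls of 0, 2, 3 or 4 years
- outcome–age correlation ρ of 0.1, 0.2 or 0.3

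Bias b = ρ × g / 4.91. The chance of a nominally significant difference when injury has no effect is 1 − Φ(1.96 − b/0.245) + Φ(−1.96 − b/0.245).

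| Age gap | ρ = 0.1 | ρ = 0.2 | ρ = 0.3 |
|---|---|---|---|
| 0 years | 0 SD; 5.0% | 0 SD; 5.0% | 0 SD; 5.0% |
| 2 years | 0.041 SD; 5.3% | 0.082 SD; 6.3% | 0.122 SD; 7.9% |
| 3 years | 0.061 SD; 5.7% | 0.122 SD; 7.9% | 0.183 SD; 11.6% |
| 4 years | 0.082 SD; 6.3% | 0.163 SD; 10.2% | 0.245 SD; 17.0% |

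The first row is the case in which matching works: omitting the age term then causes no bias. In the last cell the bias is about one standard error. The same logic applies to sex: the bias is the difference in the proportion of women multiplied by the sex difference in the outcome, and it is zero if the proportions agree.

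**Cost of adjustment.** With group and a linear activity term, 120 participants leave 120 − 3 = 117 residual degrees of freedom. Adding age and sex leaves 115.

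**The case against.** A reader might infer that the matching cannot work or does not protect the comparison. The document does not support that, for these reasons:

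- Twenty controls to 100 patients is exactly 1:5, and frequency matching on sex and age is also feasible. Only 1:1 matching of every patient is excluded.
- Recruiting by convenience and matching do not contradict each other. One describes where controls are found, the other how they are chosen.
- Nothing in the document says that the students will be younger than the patients. If the match succeeds, the bias is zero.
- A larger bias can be written down. A gap of 3–5 years at 0.02–0.10 SD per year gives 0.06–0.50 SD, or up to two standard errors. Both inputs are assumed, and 0.10 SD per year would imply a correlation of about 0.10 × 4.91 = 0.49 with age, for which the document gives no basis.
- The matching ratio and age bands are details that a condensed article may leave to the full protocol. Their absence is not a fault.
- The analysis is labelled exploratory, and the article openly states the student source.

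All of this stands. A call for BMI as a standard covariate is also open to objection. The article does not claim matching on body mass, and patients are first measured about one year after ACLR, so BMI may partly reflect the injury. Adjusting for it could remove part of the contrast of interest.

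What remains is narrower: the model that the article does state has no safeguard if the matching turns out imperfect, although the two variables needed are already recorded.

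**Conclusion.** The point holds as a low-cost improvement to an exploratory analysis. The stated ANCOVA would not remove any age or sex imbalance left by loose matching in a student-only sample. Under the assumptions above (controls 2 to 4 years younger, outcome–age correlation 0.1 to 0.3, ages uniform on 18–35), the bias is 0.04 to 0.24 SD and the false-positive rate 5.3% to 17.0%. With successful matching, the bias is zero and the only possible loss is precision. The document does not show which case will apply. The primary analysis of knee extension strength and KOOS pain does not use the controls, so it is unaffected, as is the stated sample size.

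**What to change.** - In section 2.5, name activity level, age and sex as covariates in the control ANCOVA. This guards against imperfect matching and can gain precision even where matching works.
- Use BMI, if at all, only in a sensitivity analysis, and give the reason: it is measured one year after ACLR and may partly reflect the injury.
- If the controls were not in fact selected to match the patients' age and sex distribution, drop the word *matched* in sections 2.1 and 2.5.

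The cost is a change of wording and two degrees of freedom. No additional participants or measurements are needed, and no stated figure changes.

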**Demographics**				
Sex	X	X		
Age (years)	X	X	X	X
Height (cm)	X	X		
Body mass (kg)	X	X	X	X
Primary sport	X	X		
years in primary sport	X	X		
Injured knee (left/right)	X			
Date of injury	X			
Date of reconstruction	X			
Graft type	X			
Injury situation	X			
Contact/non-contact injury	X			
Associated injuries (e.g., collateral ligament(s), meniscal injury) to the index knee	X			
Additional surgery to the index knee between the time point of ACLR and inclusion and/or during follow-up	X		X	X
Serious injury to the index knee (e.g., giving-way episode(s)) resulting in pain and/or swelling and requiring inpatient or outpatient health care between the time point of ACLR and inclusion and/or during follow-up	X		X	X
Current pain (numeric rating scale, 0 (none) to 10 (worst))	X		X	
Tegner activity scale before injury	X			
Tegner activity scale, current	X	X	X	X
OA heredity	X	X		
ACL injury heredity	X	X		
**Questionnaires**				
Knee injury and Osteoarthritis Outcome Score (all subscales)	X		X	
Short-Form 36^a^	X		X	
ACL return to sport after injury scale^a^	X		X	
ACL quality of life^a^	X		X	
Global knee function: numeric rating scale (NRS), 1 (worst) to 10 (best)	X	X	X	X
Return to sport (yes/no, level)	X		X	
Perceived Stress Scale - 10	X	X	X	X

ACLR = anterior cruciate ligament reconstruction, OA = osteoarthritis, age will be derived from the Swedish personal identity number, body mass and height will be assessed with anthropometric measures, associated injuries, additional surgeries, and additional injuries will be derived from medical records. All other measures are self-reported.

a Data collection in Lund only.

### Assessments

2.2

All predictors and outcomes will be assessed at 1 year (baseline) and at 3 years (follow-up) after ACLR. *Primary predictor* is knee extension muscle strength at baseline. *Secondary predictors* are knee flexion, hip, and trunk muscle strength, hop performance, postural orientation and patient-reported outcomes (except patient-reported pain) at baseline. *Exploratory predictor* is muscle activation pattern at baseline. *Main outcome* is the Knee injury and Osteoarthritis Outcomes Score (KOOS), subscale pain at follow-up. *Secondary outcome* is T2 (MRI) and biomarker profiles at follow-up (full description of predictors and outcomes are outlined below and in Table 1, Table 2). One physical therapist researcher will perform all functional assessments in Lund and another physical therapist researcher will perform all functional assessments in Oslo. The researchers will give standardized verbal instructions and an inter-rater reliability testing has been performed, showing moderate to excellent inter-rater reliability for all functional assessments (ICC_2*K*_ 0.66–1.0) (See Appendix A for detailed description of the reliability assessment).

**Table 2 tbl2:** Predictors and outcomes at baseline and follow up.

Predictors at baseline and follow-up for ACLR patients	Data collection instrument
**Primary predictor**	
Knee extensor muscle strength	Isokinetic strength (Nm/kg) (Biodex)
**Secondary predictors**	
Performance-based measures	Hop performance (side-hop (n), SLHD (cm)), Postural orientation errors (movement quality scoring)
Muscle strength	Isokinetic knee flexion strength (Biodex), isometric hip and trunk muscle strength (handheld dynamometer)
Patient-reported function	Questionnaires: KOOS subscales (except pain), SF-36, Tegner activity scale, ACL-RSI, ACL-QoL, Global knee function (NRS 1-10), PSS-10
**Exploratory predictor**	
Muscle activation pattern^a^	Muscle activation pattern of the hip, trunk and knee during the SLHD (electromyography)
**Outcomes at baseline and follow-up for ACLR patients and controls**	
**Primary outcome**	
Patient-reported outcome	Questionnaire: KOOS subscale pain

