#### Patient-reported outcome

2.4.1

The valid, patient-reported KOOS [35] subscale pain, scored on a 0 (worst) to 100 (best) scale will be used as a marker of symptomatic OA. In addition to the continuous measure of KOOS pain, a cut-off of will be used, where a score of ≤72 on the KOOS pain subscale will represent symptomatic knee OA and a score of >72 will represent no symptomatic knee OA, according to that previously described [9,10]. This particular cut-off is based on the normal mean (92.3 ± 10.0) KOOS pain score in an athletic population with a history of knee ligament injury and represents two standard deviations below the mean [41].

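### Tables 1 and 2 contradict each other on whether controls complete KOOS; if Table 1 is followed, the pain part of the exploratory comparison with controls cannot be estimated

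*Protocol article*

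**What the plan says.** The protocol article describes the control group's assessments in several places.

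- **Table 2 (predictors and outcomes).** The outcome block is headed "Outcomes at baseline and follow-up for ACLR patients and controls". Its first entry, the primary outcome, is "Questionnaire: KOOS subscale pain". The predictor block above it is headed for ACLR patients alone.
- **Table 1 (data collected at baseline and follow-up).** The row "Knee injury and Osteoarthritis Outcome Score (all subscales") is marked for ACLR patients at both visits and is blank for controls at both. The row "Current pain (numeric rating scale, 0 (none) to 10 (worst") has the same pattern. By contrast, "Global knee function: numeric rating scale (NRS), 1 (worst) to 10 (best") is marked in all four columns.
- **Abstract, Methods and analysis.** "Twenty non-injured individuals will also be assessed with MRI". No other control assessment is named.
- **Section 1, Introduction.** Early OA is to be assessed through patient-reported pain, MRI features and biomarker profiles. The aim then adds that "we will investigate the prevalence of early knee OA in individuals 1 and 3 years post ACLR, respectively, compared to non-injured controls".
- **Section 2.4.1.** "a score of ≤72 on the KOOS pain subscale will represent symptomatic knee OA".
- **Section 2.5.** An ANCOVA, labelled explorative, compares the presence of early knee OA between the 100 patients and the 20 controls, adjusting for activity level.

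**The concern.** The two tables give incompatible instructions on who supplies the primary outcome variable. A site working from Table 1 would not hand KOOS to a control. An analyst working from Table 2 would expect to find it in the data.

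The patient-versus-control comparison of early OA is at stake. Patient-reported pain is one of the three ways in which the Introduction says early OA is assessed, and the KOOS cut-off is the only rule in the article that sorts a person into OA or no OA. Without KOOS in controls, that part of the comparison has data on one side only.

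**Working it through.** **Step 1: the cut-off.** Section 2.4.1 gives a reference mean of 92.3 with SD 10.0 and places the threshold two SDs below: 92.3 − 2 × 10.0 = 72.3. The stated 72 is reproduced. It is defined on KOOS pain alone, so a person without KOOS pain cannot be classified.

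**Step 2: the Table 1 rows side by side.**

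| Table 1 row | Patients, baseline | Controls, baseline | Patients, follow-up | Controls, follow-up |
|---|---|---|---|---|
| KOOS, all subscales | X | – | X | – |
| Current pain, NRS | X | – | X | – |
| Global knee function, NRS | X | X | X | X |
| Perceived Stress Scale-10 | X | X | X | X |
| Tegner, current | X | X | X | X |

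Three rows are filled in all four columns, so the control columns were read correctly and the blanks carry information. Neither row that measures pain is marked for controls.

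**Step 3: count the control records of KOOS pain.**

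- Under Table 1: 0 of 20 at baseline and 0 of 20 at follow-up.
- Under Table 2: 20 of 20 at each visit, before any drop-out.

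With 0 of 20, neither a difference in mean KOOS pain nor a difference in the proportion at or below 72 can be estimated.

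**Step 4: what the comparison could show if KOOS were collected.**

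- *Mean difference.* For two-sided 5% and 80% power, the detectable standardised difference is (1.960 + 0.842) × √(1/100 + 1/20) = 0.69. With 85 patients remaining after 15% drop-out it is 0.70. Sidedness is assumed, as the article does not state it, and covariate adjustment is ignored.
- *Proportion at or below 72.* Assume, for illustration, that controls follow the reference distribution and that it is normal (KOOS is bounded, so this is rough). Then P(≤72) = Φ((72 − 92.3)/10.0) = Φ(−2.03) ≈ 0.021. Expected control cases are 20 × 0.021 ≈ 0.4, and the chance of none is (1 − 0.021)^20 ≈ 0.65.

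The data would therefore serve mainly for a mean difference. The control proportion would probably be zero or close to it.

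**Step 5: what is untouched.** The sample size in section 2.5 rests on a correlation of 0.30 within ACLR patients. By Fisher's z, n = ((1.960 + 0.842)/atanh(0.30))² + 3 = 84.9, in line with the stated 84. Allowing for drop-out, 84/0.85 = 98.8, in line with the 100 enrolled. Controls play no part in this calculation or in the primary regression, and Table 1 marks KOOS for patients at both visits.

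**The case against.** The strongest reply is that the control group was meant for imaging and that the only error is an over-broad heading in Table 2. The abstract names only MRI for controls. Table 1 collects current Tegner in them, which can supply the activity covariate the ANCOVA needs. ANCOVA also suits a continuous measure such as mean T2 better than a yes/no cut-off. Neither the aim nor section 2.5 mentions KOOS or the threshold of 72 when it speaks of controls. This reading is plausible and cannot be ruled out. It does not remove the contradiction: Table 2 names controls explicitly, and the Introduction includes patient-reported pain in its account of early OA. It does mean that a wording change may be the right repair.

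A reader might infer three stronger things that the documents do not support.

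- *That the control comparison as a whole cannot be done.* The article does not say which table governs. Even under Table 1, T2 can be compared, as can serum markers if they are drawn in controls as Table 2 says.
- *That a missed KOOS is lost for good.* Controls had no reconstruction and so have no one-year post-surgical time point. A KOOS taken later, for example at the planned follow-up visit, could still give a reference value, though not a baseline one.
- *That the trial's primary result is threatened because the primary outcome is missing in a group.* The primary analysis does not use that group.

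It is also fair to say that KOOS in 20 uninjured students would add little on the proportion at or below 72, as Step 4 shows. The mean comparison would still be informative.

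**Conclusion.** The point holds as an internal contradiction of moderate severity. Tables 1 and 2 cannot both be right about KOOS in controls.

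The consequence is conditional. If Table 1 is the working schedule, 0 of 20 controls have a pain measure, and the patient-reported-pain component of the comparison with controls cannot be estimated at either visit. If Table 2 is right, the comparison is possible and the error is two missing marks in Table 1.

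Treating pain as part of the control comparison rests on the Introduction's description of early OA. Sections 1 and 2.5 do not name KOOS for controls. The effect is confined to an analysis labelled explorative, in a convenience sample of 20.

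**What to change.** State which table governs and bring the other into line.

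- **Preferred:** mark KOOS, at least the pain subscale, for controls at baseline and follow-up in Table 1, and mention it beside MRI in the abstract. The cost is one short questionnaire for 20 people who already complete others at both visits.
- **If KOOS was not collected in controls:** remove controls from the KOOS row of Table 2. Restrict the control comparison in sections 1 and 2.5 to the outcomes actually measured in them (T2, and serum markers if drawn), and make no claim about KOOS-defined OA relative to controls. The cost is a wording change.

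Neither option alters the primary analysis or the sample size.
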